### Sample size calculation

2.8.

This study is a multicentre, prospective, randomized controlled trial. According to the pretest, the mean ± standard deviation of the perioperative cumulative hypothermia effect value (*Σ Δ*T_i_ × *Δ*t_i_, i = 1…, *n*) under passive warming measures is 12.2 ± 4.31, and using perioperative active warming strategies, it can be decreased by 15%. Considering a dropout rate of 20%, 400 subjects will be required with 90% power and an *α* level of 0.05. The sample ratios of the four centres are *Q*_1 _= *Q*_2 _= *Q*_3_= *Q*_4 _= 1/4N = 100.

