### Interim analysis

2.9.

This trial will conduct interim analysis when the sample size reaches 50% to compare the effect and safety between the two groups by preserving the sample size as much as possible. The interim analysis will be supervised by the independent data management committee (DMC). Except for the researchers directly involved in the interim analysis, other researchers in this trial will still be blinded to the allocation information. The trial will use the Lan-DeMets alpha spending function with an O'Brien-Fleming boundary to correct the test level of interim analysis, and the effective test level to terminate the trial is *p* < 0.003.

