### Statistical analysis

2.11.

Statistical analysis will be performed by SPSS software, version 24. (International Business Machines Inc., USA). Continuous variables will be reported as the mean ± standard deviation ($\bar{x}\pm s$) or medians and interquartile ranges. Categorical variables will be presented as numbers (proportion, %). The Kolmogorov-Smirnov test will be performed to detect the normal distribution of continuous variables. Student's t test will be used for normally distributed continuous variables, and the Kruskal-Wallis H test will be used for abnormally distributed data. The grade variables will be analysed using the Mann-Whitney U test. The chi-square test and Fisher's exact test will be used to analyse categorical variables. Repeated measures analysis of variance will be applied for the analysis of repeated measures data. *p* < 0.003 is defined as statistically significant in interim analysis, and the statistical significance of the final analysis is set at *p* < 0.05.

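### The final analysis is tested at the full 0.05 although the interim look has already spent 0.003, so the overall two-sided type I error is 0.051, not 0.05

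*Protocol article*

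**What the plan says.** Three sections of the protocol article bear on this point.

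- **Sample size calculation (2.8)** sets the overall error rate: "400 subjects will be required with 90% power and an *α* level of 0.05".
- **Interim analysis (2.9)** plans one look: "This trial will conduct interim analysis when the sample size reaches 50% to compare the effect and safety between the two groups". The method is named: "The trial will use the Lan-DeMets alpha spending function with an O'Brien-Fleming boundary to correct the test level of interim analysis". The look can end the trial: "the effective test level to terminate the trial is *p* < 0.003".
- **Statistical analysis (2.11)** repeats 0.003 as the interim level and adds that "the statistical significance of the final analysis is set at *p* < 0.05".

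No section gives a reduced level for the final analysis.

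**The concern.** An alpha spending function fixes how much of a single overall error rate has been used by each look. Alpha used at the interim is no longer available at the end. Section 2.9 applies the function to the interim level only, and section 2.11 gives the final test the whole 0.05. The two sections together therefore do not carry out the named method.

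At stake is the decision rule. Section 2.11 sets no separate level for the primary outcome, so 0.05 applies to it. As written, the trial does not hold the alpha on which it was sized, and a final p between 0.049 and 0.05 would be called significant when the named method says it is not.

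**Working it through.** **Inputs**

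- Overall alpha 0.05 (2.8). Sidedness is not stated; two-sided is assumed and tested in step 1.
- One look at information fraction t = 0.5 (2.9).
- Interim level 0.003 (2.9 and 2.11); final level 0.05 (2.11).
- For the power cost: a control mean and SD that "under passive warming measures is 12.2 ± 4.31", a 15% decrease, 20% dropout and 90% power (2.8), with 1:1 allocation (2.5).

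**Step 1. Reproduce the interim level.** The O'Brien-Fleming-type spending function, per side with α = 0.025, is

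α(t) = 2[1 − Φ(z(1−α/2)/√t)].

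At t = 0.5, z(0.9875) = 2.2414 and 2.2414/√0.5 = 3.170. Doubling for two sides:

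4[1 − Φ(3.170)] = 0.00305, or |z| > 2.963.

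This rounds to the stated 0.003. Spending a one-sided 0.05 would give about 0.0056 instead, so the protocol's figure fits a two-sided 0.05.

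**Step 2. Overall type I error as written.** Under the null, the interim and final statistics Z1 and Z2 are standard bivariate normal with correlation √0.5 = 0.707. The trial claims an effect if |Z1| passes the 0.003 boundary or |Z2| > 1.960:

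1 − P(|Z1| < z1 and |Z2| < 1.960) = 0.05097, or 0.0510.

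A simulation of 20 million draws also gave 0.0510. The simple sum, 0.003 + 0.05 = 0.053, overstates it because the looks are correlated: 0.053 − 0.05097 = 0.00203 of the null probability is counted at both looks.

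If 0.003 and 0.05 are kept but the look falls elsewhere:

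| Information at the look | Overall two-sided error |
|---|---|
| 40% | 0.0514 |
| 50% | 0.0510 |
| 60% | 0.0506 |

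**Step 3. Final level that restores 0.05.** Solve 1 − P(|Z1| < z1 and |Z2| < z2) = 0.05 for z2. With 0.003 or 0.00305 at the interim, the final nominal two-sided level is 0.0490 (|z| > 1.968).

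**Step 4. Cost of the correction.** The difference is 0.15 × 12.2 = 1.83, and 1.83/4.31 = 0.425 SD. After 20% dropout, 400 × 0.8 / 2 = 160 children per arm remain. By the normal approximation for the final test:

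| Final level | Power at 160 per arm | n per arm for 90% power |
|---|---|---|
| 0.05 | 96.7% | 117 |
| 0.049 | 96.6% | 118 |

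**The case against.** The strongest objection is size. The excess error is about 0.001 and stays near that if the look moves to 40% or 60%. The final p falls between 0.049 and 0.05 in about 0.1% of trials under the null. Under the planned effect with 160 per arm the figure is about 0.06% (96.69% − 96.63%). Sample size and conduct are untouched. All of this stands.

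Other objections carry less weight:

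- **Rounding.** The interim level is printed to one significant figure, and 0.0490 at that precision prints as 0.05. But 0.05 is also the alpha in section 2.8, so an unadjusted level is the likelier reading. A reader applying the rule would use 0.05 either way.
- **Scope of the sentence.** It closes a paragraph on all variables and does not single out the primary outcome. Only the primary test needs the adjusted level. But no other level is given for that test, so 0.05 governs it.
- **Purpose of the look.** The inflation arises only if an early stop counts as a claim of benefit, and section 2.9 does not say which endpoint or direction triggers stopping. That section does compare effect as well as safety, and section 2.11 treats 0.003 as the interim level of significance. Efficacy stopping is the natural reading.
- **Left to the analysis plan.** This would answer a final level left open. The article prints a specific number, and it conflicts with the method the article names.

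**Conclusion.** The point holds. The interim level is correct for the named function, but the final level is not. The overall two-sided type I error is 0.0510 against a stated 0.05, and the matching final level is 0.0490.

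This assumes a two-sided test, a single look at 50% information, information proportional to the number of children analysed, approximately normal test statistics, and an interim rejection that counts as an efficacy claim.

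The practical effect is very small. The point still needs correcting because the decision threshold is wrong as written and the correction costs almost nothing. It must be made before the data are seen.

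**What to change.** In section 2.11, replace the single final level with wording such as: *The primary outcome will be tested at the final analysis at the two-sided level given by the Lan-DeMets O'Brien-Fleming function for an overall alpha of 0.05. This is p < 0.049 if the interim takes place at 50% information, and it will be recalculated from the actual information fraction otherwise.* Secondary outcomes can keep their own nominal level if the text says so.

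In section 2.9, say that the function governs both looks, that the overall alpha is two-sided, and that the 0.003 level applies to the primary outcome. If the look does not fall at 50%, the interim level also has to be recalculated: the function spends 0.0008 at 40% and 0.0076 at 60%.

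The cost is a short text change, less than 0.1 percentage point of power at 160 per arm, and no increase in the planned 400.

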## Discussion

3.

This trial aims to verify the feasibility and thermal insulation effect of perioperative active warming strategies by comparing them with traditional passive warming measures to further improve the prognosis of paediatric patients. The primary outcome is the perioperative cumulative hypothermia effect value (*Σ Δ*T_i_ × *Δ*t_i_, i = 1…, *n*), which is chosen because it can better quantify the level of IPH and can more effectively reflect the differences between the two groups. In addition, we combine multiple secondary outcomes to comprehensively analyse the prognosis, which will provide more clinical evidence about active warming strategies.

This study also has some limitations. First, we do not limit the surgery to a single category, which could be a confounding factor. However, considering the desire to validate the generalisability of the active warming strategy in this study, we wanted to cover a relatively wide range of types of paediatric procedures. Second, the population included in this study is children aged 1–12 years, who have a wide variation in age and growth. A stratified analysis will be conducted on children in different age levels. Third, this trial will perform perioperative real-time temperature monitoring with an axillary temperature sensor. Although the core body temperature is closer to the real temperature, awake children might not tolerate this method of temperature monitoring. Axillary temperature monitoring is relatively accurate and easy to tolerate, and we can additionally measure the nasopharyngeal core body temperature after anaesthesia induction for correction.
